**CHRONOGRAM AND WORK PLAN**

Months 1: Involvement of professionals in the project and training of clinical psychologists in group psychological treatment through a workshop conducted by experts from the Spanish Society for the Study of Anxiety and Stress (SEAS), under the supervision of [name] [name].

Months 2-11: Recruitment of patients (progressive over 10 months) by GP in Health Centres, randomisation, implementation of therapy groups and evaluations by clinical psychologists, data collection.

Months 10-12: Completion of data collection and analysis and generation of draft articles. Dissemination of preliminary project data at national and international conferences.

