**Primary purpose:**

Test cost-effectiveness and cost-utility of transdiagnostic cognitive-behavioural treatment versus relaxation therapy in Cantabria Primary Care Centres at posttreatment and 12-month follow-up.

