**Outcome Measures**

Primary Outcome Measures:

- Change in cost-effectiveness data [Time Frame: Baseline, immediately after the intervention, and 12-month follow-up]

Cost-effectiveness results will be calculated by the ICER, defined as the difference in mean costs between interventions divided by the difference in their effectiveness according to the symptom questionnaires’ mean scores.

The healthcare data collected will be used for cost calculations. To calculate healthcare-related costs, an ad hoc questionnaire will be used to collect emotional disorder-related healthcare data (public and private healthcare consultations, accidents, medical tests, and sick leaves in the past 3 months; psychotropic drugs or other medication, and their posology).

- Change in cost-utility data [Time Frame: Baseline, immediately after the intervention, and 12-month follow-up]

Cost-utility will be measured through the healthcare data collected above and the European Quality of Life Scale (EuroQoL, EQ) [71], calculating the QALYS and the ICURs, defined as the difference in mean cost divided by the difference in mean QALYs. The Spanish version of the 5-domain, 5-level EuroQol (EQ-5D-5L) [72,73] will be used to assess health status in five dimensions (mobility, self-care, daily activities, pain/unease, and anxiety/depression) with five levels of severity (no problems, slight problems, moderate problems, severe problems, and either extreme problems or unable to perform activity). The scores obtained in the different dimensions can be combined to create a 5-digit code describing the patient's state of health, being able to stablish up to 3125 different combinations, and therefore, different possible health states. This system was converted into a utility score using the value set for Spain from the EQ-5D-5L Crosswalk Index Value downloaded from the EuroQol website (<https://euroqol.org/euroqol/>).

Secondary Outcome Measures:

- Change in depressive symptoms: Patient Health Questionnaire - 9 item (PHQ-9) [Time Frame: Baseline, immediately after the intervention, and 12-month follow-up]

The PHQ-9 [54] is the depression module of the PHQ [74, 75] that scores the 9 DSM-IV depression criteria in the last two weeks. Is a nine item, self-report scale that ranges from 0 to 27 (higher scores means a worse outcome).

- Change in anxiety symptoms: Generalized Anxiety Disorder - 7 item (GAD-7) [Time Frame: Baseline, immediately after the intervention, and 12-month follow-up]

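### The work plan completes data collection and analysis by month 12, before any patient can reach the 12-month primary time point

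*Protocol*

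**What the plan says.** The protocol's Chronogram and Work Plan has three entries.

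- Month 1 is preparation only: "Months 1: Involvement of professionals in the project and training of clinical psychologists in group psychological treatment through a workshop".
- Recruitment comes next: "Months 2-11: Recruitment of patients (progressive over 10 months) by GP in Health Centres". The same entry covers randomisation, therapy groups and evaluations.
- The last entry reads "Months 10-12: Completion of data collection and analysis and generation of draft articles", and adds "Dissemination of preliminary project data at national and international conferences".

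No entry mentions a 12-month assessment, and the calendar stops at month 12.

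The Primary purpose section sets the comparison "at posttreatment and 12-month follow-up". Under Outcome Measures the two primary outcomes carry the same time frame: "Change in cost-effectiveness data [Time Frame: Baseline, immediately after the intervention, and 12-month follow-up" and "Change in cost-utility data [Time Frame: Baseline, immediately after the intervention, and 12-month follow-up". The Abstract repeats both time points and adds the hypothesis that gains last to 12 months. The Statistical analysis section makes the primary analyses intention-to-treat, with everyone who entered kept in the assigned group.

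**The concern.** The calendar and the primary outcome cannot both be followed. A plan that recruits from month 2 and finishes collecting and analysing data by month 12 leaves no room for a 12-month visit, which is one of the two post-baseline primary time points. The other, post-treatment, is cut short for patients who enter late.

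If staff, assessors and funding are planned from the calendar, the 12-month cost-effectiveness and cost-utility ratios cannot be calculated and the durability hypothesis cannot be tested. An analysis at month 12 would also lack post-treatment outcomes for part of the randomised sample, contrary to the intention-to-treat principle that the protocol adopts.

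**Working it through.** **Inputs**

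- Recruitment: start of month 2 to end of month 11, which is elapsed time 1.0 to 11.0 months (Chronogram).
- End of data collection and analysis: end of month 12, elapsed 12.0 (Chronogram).
- Treatment length: 12 weeks in the trial description and the table of arms, but 24 weeks in the two treatment sections. Both are carried through.
- Sample size: 300 (Sample size section).
- Conversion: 365.25 / 12 / 7 = 4.348 weeks per month, so 12 weeks = 2.76 months and 24 weeks = 5.52 months.

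**The plan's own figure.** Recruitment lasts 11.0 − 1.0 = 10 months, which agrees with the text.

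**12-month time point.** Longest possible observation = 12.0 − entry time.

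- First patient: 12.0 − 1.0 = 11.0 months.
- Last patient: 12.0 − 11.0 = 1.0 month.

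The maximum, 11.0, is below 12, so 0 of 300 can reach the visit. This needs no assumption about accrual, treatment length or the origin of the 12 months. It follows from the month-2 start set against the month-12 end. Recruiting until month 11 only widens the gap for later patients.

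**When the visits would fall.** Visit time = entry + 12, plus the treatment length if the 12 months run from the end of treatment. The protocol does not state the origin.

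| Origin of the 12 months | First visit (elapsed) | Last visit (elapsed) |
|---|---|---|
| Baseline | 1 + 12 = 13.0 | 11 + 12 = 23.0 |
| End of 12-week course | 1 + 2.76 + 12 = 15.8 | 11 + 2.76 + 12 = 25.8 |
| End of 24-week course | 1 + 5.52 + 12 = 18.5 | 11 + 5.52 + 12 = 28.5 |

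The last visit therefore falls at the end of month 23, in month 26 or in month 29.

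**Post-treatment visit.** Assume uniform accrual and treatment starting on the day of entry. Share reached by month 12 = (12 − treatment length − 1) / 10.

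- 12 weeks: (12 − 2.76 − 1) / 10 = 0.824, about 247 of 300.
- 24 weeks: (12 − 5.52 − 1) / 10 = 0.548, about 164 of 300.

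These are upper bounds, because treatment is given in groups and a group has to fill first. As an illustration, assume groups of 10 and the four centres named in the Abstract, recruiting equally. Accrual is then 300 / 10 / 2 / 4 = 3.75 patients per arm, centre and month, and the mean wait is about 4.5 / 3.75 = 1.2 months. Subtracting that wait gives roughly (12 − 2.76 − 1.2 − 1) / 10 = 70% and (12 − 5.52 − 1.2 − 1) / 10 = 43%.

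**The case against.** The strongest reply is that the work plan is a summary timetable and cancels no visit. The Abstract, the primary purpose and the outcome section all prescribe the 12-month assessment, and sites may simply follow them. This stands to a point. A reader might infer that the 12-month data will never be collected, but the documents do not say so; they give two instructions that cannot both be followed. It does not remove the contradiction, since no section reconciles them. The word for preliminary data does not help either: it qualifies the conference presentations, while the sentence before it speaks of completing collection and analysis.

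Two further inferences go beyond the text.

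- A reader might infer that results by arm will be shown during follow-up and undo the blinding. The chronogram speaks only of project data and does not say that they are comparative. Aggregate results would not reveal one patient's allocation to an assessor, and therapists already know which arm they deliver. What remains is a conditional risk of changed expectations in a trial with self-reported symptom outcomes.
- A reader might infer that a month-12 analysis would be biased because it holds only early recruits. With concurrent randomisation a calendar cut-off removes late entrants from both arms alike. It costs precision and perhaps representativeness, but does not by itself bias the comparison between arms.

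**Conclusion.** The contradiction is real and wrong as written; it is not detail left for a later document. Within the stated schedule no patient can reach the 12-month primary time point, whichever treatment length or origin is used.

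Post-treatment outcomes would be missing at month 12 for at least about 18% of patients (12-week course) or 45% (24-week course). Those shares rest on uniform accrual and on treatment starting at entry, and they grow if groups must fill first. An analysis at that date would not have the outcome data that the intention-to-treat principle calls for.

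The documents do not establish lost visits, unblinding or a biased comparison between arms. The finding needs none of these. It should be corrected before the calendar is used to plan the study.

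**What to change.** Reconcile the chronogram with the Abstract, the Primary purpose and the Outcome Measures:

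1. State whether the 12 months run from baseline or from the end of treatment.
2. Add an entry for the 12-month follow-up and extend data collection to the last such visit: the end of month 23 from baseline, or about month 26 or 29 from the end of a 12- or 24-week course.
3. Let the therapy and post-treatment entries run past month 11. The last post-treatment visit falls at elapsed 11 + 2.76 = 13.8 or 11 + 5.52 = 16.5 months.
4. Place the final analysis and the articles after the last 12-month visit.
5. As a precaution, say that anything presented before then contains no outcome results compared between arms.

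The sponsor must reconcile the 12- and 24-week treatment lengths separately. That conflict changes the size of the gap but not its existence.

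The visits are already part of the outcome plan, so the amendment itself is small. The real cost is a project about 11 to 17 months longer (23 − 12 = 11; 28.5 − 12 = 16.5), with follow-up staff to match, and later publication.

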**APPLICABILITY AND USEFULNESS OF THE RESULTS AND ABILITY TO BE PROTECTED AND TRANSFERRED TO THE MARKET**

The planned clinical trial will provide clear evidence that, compared to treatment through relaxation, the incorporation of a group treatment for mental disorders commonly treated in Health Centres helps to reduce anxious, depressive and somatic symptomatology, as well as a reduction in the costs (direct and indirect) associated with anxiety, mood and somatoform disorders (Main hypothesis). PsicAP-Costs2 allows an immediate transfer of the results to the clinical context by providing the first experience in our context of a manualised transdiagnostic group treatment of short duration (7 sessions), which makes it easily applicable and generalizable to health centres in Cantabria and the rest of the NHS. The expected economic benefit in the reduction of psychopharmacological treatment costs and through the reduction of expenditure on sick leave and loss of productivity, which is a priority objective of the SCS in the management of TI associated with common mental disorders (Mental Health Plan of Cantabria 2015-2019), should make the dissemination among health professionals of this type of protocolised treatment, low cost and short duration, easily integrated into the routine care offered in Health Centres, profitable.

**Sponsors and Collaborators**

Instituto de Investigación Sanitaria Valdecilla (IDIVAL)

Agencia Estatal de Investigación

